#### 2.6.2. Analysis of secondary outcome

As quality of life, treatment burden, and patients’ medication risk score all follow a Likert scale, we will use beta-binomial regression. The beta-binomial assumes our outcome follows a binomial distribution where the probability of landing in a given category follows a beta distribution to account for over-dispersion. As both outcomes are measured at different time points and the beta-binomial regression uses a maximum likelihood estimation, we will adopt the same test and manage missing data similarly to the primary analysis. In order to get interpretable effect sizes, we will use G-computation, where the Q-model will be a linear regression.

Our follow-up time is 30 days, so we will conduct a binomial regression to calculate the risk difference. Furthermore, we will view the above-mentioned secondary outcomes as time-to-event outcomes. Hence, we will use the Cox-proportional hazard model to ensure that our results are not dependent on the length of our study. The proportional hazard assumption will be graphically assessed using scaled Schönfeld residuals. Binomial regression is the primary analysis applied, while Cox regression is a sensitivity analysis.

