#### 2.3.3. Secondary outcome

The secondary outcomes are patient-reported outcomes about quality of life and treatment burden after 3 months, but also patient’s readmissions, and contact to the ward after 30 days. The patient’s MERIS score is calculated to estimate if a medication review could change the MERIS score and reduce the probability of experiencing a drug-related problem.

*2*.*3*.*3*.*1*. *Patient-reported outcome*. To measure patient-reported outcomes regarding the quality of life and treatment burden, the *EuroQol-5* Domain (EQ-5D) and Multi-morbidity Treatment Burden Questionnaire (MTBQ) are used [55,57]. The questionnaires are combined with a Visual Analogue Scale (VAS) regarding quality of life and treatment burden as validation. VAS assessment of subjective phenomena will be converted to numerical data [60].

The patients will fill out EQ-5D, EQ-VAS, MTBQ, and the two VAS’s at inclusion and hospital discharge. The same questionnaires are answered three months after hospital discharge, either by e-mail or telephone, conducted by the first author.

EQ-5D contains five questions regarding five domains: mobility, self-care, usual activities, pain/discomfort, and anxiety/depression, each with five answer categories: no problems, slight problems, moderate problems, severe problems, and extreme problems. Permission to use the Danish EQ-5D version has been granted by EuroQol [61].

The EQ-VAS is a vertical VAS in which patients report their perceived quality of life from 0–100 [61]. The endpoints are labelled with “*The worst health you can imagine*” (0) and “*The best health you can imagine*” (100) [61]. These measurements are used to quantify a health outcome that reflects the patient’s perception.

An additional VAS regarding quality of life is added to validate if the VAS can be applied instead of a questionnaire. The questionnaire used for the validation is the ED-Q5.

The VAS is vertical and ranges from zero (lowest quality of life) to 100 (highest quality of life) by numbers. The question asked is: “How is you quality of life today?” The endpoints are labelled with “*The worst quality of life you can imagine*” (0) and “*The highest quality of life you can imagine*” (100).

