*2*.*3*.*3*.*4*. *Patients’ Medication Risk Score*. The patient’s MERIS will be calculated at inclusion and hospital discharge using the Software Robot Sirenia Manatee [31,37]. The MERIS algorithm provides a score reflecting the risk of probability for the patients experiencing a serious drug-related problem [37]. The MERIS score is calculated for all patients included in the study to assess which patients would benefit most from a medication review. The calculation is based on the patients’ most recently measured, estimated glomerular filtration rate value, the number of medications, and the risk of a drug to cause harm or interactions. The medications with risk for harm or interactions are described in the literature [29,65,66]. Data will be collected via EPJ.

*2*.*3*.*3*.*5*. *Follow-up after discharge*. In the follow-up conversation between the patient and the Medication Coordinator, data about which medication(s) and which topic regarding the medications(s) are collected. Furthermore, data about the usage of *My Medication Plan* are collected to be used in the reporting of the feasibility of the complex intervention.

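### The stated Likert basis for beta-binomial regression fails for MERIS, and the secondary tests and effect sizes come from two different models

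*Protocol article*

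**What the plan says.** Section 2.6.2 gives one justification and one model for three secondary outcomes (quality of life, treatment burden and MERIS): "medication risk score all follow a Likert scale, we will use beta-binomial regression". It spells out the assumption: "The beta-binomial assumes our outcome follows a binomial distribution where the probability of landing in a given category follows a beta distribution".

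For testing and missing data it refers back to the primary analysis: "we will adopt the same test and manage missing data similarly to the primary analysis". Under section 2.6.1 that means a global test, then multiplicity-adjusted z-tests at each time point, and a claim that maximum likelihood is unbiased when data are missing at random.

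For the effect that readers will see, it changes model: "we will use G-computation, where the Q-model will be a linear regression".

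Section 2.3.3 describes the scales:

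- EQ-5D has five items, "each with five answer categories: no problems, slight problems, moderate problems, severe problems, and extreme problems".
- "The EQ-VAS is a vertical VAS in which patients report their perceived quality of life from 0–100". Two further visual analogue scales, for quality of life and treatment burden, also run from 0 to 100.
- MTBQ has ten items, each scored 0 to 4.
- MERIS is computed by software from the latest "estimated glomerular filtration rate value, the number of medications, and the risk of a drug to cause harm or interactions".

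**The concern.** There are two faults, and both lie in what the article states rather than in what it leaves out.

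First, the reason given for the model does not match the article's own account of the data. A beta-binomial describes an integer between 0 and a known maximum. If MERIS has no known maximum, the analyst must supply one, and the stated rule cannot be followed as written.

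Second, the test and the effect size answer to different models. Section 2.6 promises 95% confidence intervals and two-sided p-values judged at 5%, so a reader will expect an interval that excludes zero to go with p below 0.05. With the p-value from a beta-binomial likelihood and the interval from a linear regression, that link is lost. A report could show a significant test beside an interval that covers zero, or the reverse, with no rule for which one counts. The missing-at-random argument is also made for a model that does not produce the reported estimate.

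**Working it through.** The article gives no figure for this point to reproduce. Its power statement concerns the primary outcome. The check has three steps.

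**Step 1: the scales against the assumption** (descriptions from section 2.3.3)

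| Measure | Range in the article | Likert-type? | Denominator available? |
|---|---|---|---|
| EQ-5D | 5 items, 5 ordered levels | items yes | depends on the score used, not stated |
| EQ-VAS | 0–100 | no | yes, 100 if scored in integers |
| Added quality-of-life VAS | 0–100 | no | yes, 100 |
| MTBQ raw sum | 10 × 4 = 40, so 0–40 | items yes | yes, 40 |
| Added treatment-burden VAS | 0–100 | no | yes, 100 |
| MERIS | algorithm score, no maximum given | no | none in the article |

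Four of the six measures have a fixed range. The Discussion adds only a MERIS cut-off of 13, which is not a maximum.

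**Step 2: what linear G-computation returns**

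Let the Q-model be E(Y) = a + b·arm + c·X, without an arm-by-covariate interaction. Predict every patient under each arm and average the difference:

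(1/N) Σ [(a + b + c·Xᵢ) − (a + c·Xᵢ)] = b.

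The standardised effect is the linear regression's own arm coefficient. With an arm-by-time term dₜ it is b + dₜ at time t. No quantity from the beta-binomial fit enters. The primary analysis differs here: section 2.6.1 draws its estimates and margins plot from the tested model.

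**Step 3: how often the two verdicts differ**

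From the article: 70 patients per group and two-sided 5%. Assumed: the distributions and effects below, one time point and complete data. The beta-binomial likelihood-ratio test was compared with a t-test of the mean difference, with 300 simulated trials per row (200 for MERIS). Inputs, control v intervention:

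- MTBQ-like, 0–40, precision 4: mean proportion 0.20 v 0.20 (no effect), or 0.25 v 0.17 (effect).
- MTBQ-like with excess zeros: beta(1.5, 4) on 0–40, with 20% v 35% extra zeros.
- VAS: normal, means 58 v 65, SD 20, rounded to tens and cut at 0 and 100.
- MERIS-like: negative binomial, means 17 v 14, size 6, with an assumed maximum of 60, 100 or 500.

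| Scenario | Reject, beta-binomial | Reject, linear | Verdicts differ | Mean difference, beta-binomial | Mean difference, linear |
|---|---|---|---|---|---|
| MTBQ-like, no effect | 4.7% | 5.7% | 3.0% | −0.12 | −0.12 |
| MTBQ-like, effect | 75.7% | 67.3% | 14.3% | −3.10 | −3.08 |
| MTBQ-like, excess zeros | 45.7% | 23.0% | 24.7% | −2.31 | −1.55 |
| VAS heaped at tens | 56.3% | 56.7% | 14.3% | 7.75 | 7.14 |
| MERIS-like, maximum 60 | 65.0% | 66.0% | 7.0% | −2.89 | −3.05 |
| MERIS-like, maximum 100 | 65.5% | 66.0% | 9.5% | −2.89 | −3.05 |
| MERIS-like, maximum 500 | 65.5% | 66.0% | 10.5% | −2.90 | −3.05 |

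Simulation error is modest: √(0.247 × 0.753 / 300) = 2.5 percentage points for the largest disagreement and √(0.03 × 0.97 / 300) = 1.0 point for the smallest.

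In the excess-zeros row the true difference is 40 × 1.5/5.5 × (0.65 − 0.80) = −1.64. The linear estimate is close to it and the beta-binomial estimate is not. The two estimates had opposite signs in 9% of those trials. Excess zeros are plausible for MTBQ, because section 2.3.3.1 scores both the no-difficulty answer and the not-applicable answer as 0.

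**The case against.** A reader might infer that most of these scores are not bounded counts, so that beta-binomial regression is unusable for everything except MTBQ. The article does not support that. The three visual analogue scales and the MTBQ sum have a known maximum and can be scored as integers, which is all the model needs mechanically. A fractional EQ-5D index would not fit, but the article mentions no such index, and a sum of item levels would fit. Which score is used can properly be left to a fuller document. Section 2.6.2 does not name the two added scales, which section 2.3.3.1 introduces mainly to see whether they could replace the questionnaires.

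Three further defences deserve weight. The MERIS maximum may appear in the sources the article cites; that stands, and it limits the point to the article giving no denominator. The choice of maximum hardly moved the MERIS-like results (differences of −2.89 to −2.90), so the fault is an undefined model and a wrong premise, not a demonstrated swing in the result. And a linear outcome model is not invalid in itself: under randomisation with complete data it estimates the mean difference consistently, in scale points that readers understand. That also stands, and the two estimates nearly coincided when the beta-binomial was true. It does not remove the mismatch, because verdicts still differed in 14.3% of those trials.

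**Conclusion.** The point holds in two parts.

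1. The statement that all three outcomes follow a Likert scale is wrong for MERIS on the article's own description, and the article gives no denominator with which to fit the stated model to it. It is also wrong as a description of the 0–100 scales, although those can still be fitted.
2. If the plan is followed exactly, the p-value and the effect size for each of these scores come from different models and can disagree. The likelihood-based missing-data argument does not automatically extend to the linear regression; it would have to be made for that model and its covariates.

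The size is 3% to 25% of trials with differing verdicts. This rests on assumed distributions and effects, one time point, complete data and a t-test standing in for the linear analysis. It shows that the disagreement can matter; it does not forecast its rate in this trial. The primary outcome is untouched, so this should be corrected but does not threaten the trial's main conclusion.

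**What to change.** In section 2.6.2:

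- Remove the Likert statement for MERIS and the visual analogue scales, and justify the model by each scale's own range.
- Analyse MERIS with a model that needs no fixed maximum, for example a linear model with robust standard errors clustered on patient.
- For each secondary score, take test, estimate and confidence interval from one fit. Where beta-binomial is kept, for example for the MTBQ sum, let the G-computation standardise that same beta-binomial fit instead of a separate linear regression.
- State the missing-data argument for the model that produces the reported estimate.

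One caution: a single fit makes test and estimate consistent but does not make a poorly fitting model right. If many MTBQ scores are zero, the check above suggests that a standardised beta-binomial can misstate the mean difference. The choice for that scale should therefore be settled, with this in mind, before unblinded data are seen.

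The cost is a change of wording and some adaptation of the analysis code. No new data are needed.

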### 2.7. Data management

The data collected will be stored in accordance with the Danish Law about General Data Protection Regulation (GDPR). All data will be stored and processed with the online-based Research ElectronicDataCapture system (REDCap) (version 13.7.18) [70] through Odense Patient Data Explorative Network (OPEN) [72]. The data storage via OPEN and REDCap is compatible with the Danish Code of Conduct for Research Integrity [73]. REDCap databases are used to register all data about patient demographics, medication lists, randomization, and answers from the three questionnaire. Only individuals with permission will be allowed to access the patient databases.

This study will share data in accordance with the FAIR principles [74]. Data obtained about medication can be accessed through Danish Registers and, therefore, will not be made public to ensure anonymity and confidentiality. The Do-files from STATA/BE version 18 and R scripts made during the statistical analysis will be shared as Metadata.

### 2.8. Ethics

The study was registered with Clinical Trials with the trial number NCT06383364 [75]. Amendments to the protocol will be communicated to ClinicalTrials.gov.

No ethics approval was needed for this study, according to the Region of Southern Denmark’s Scientific Ethics Committee, case number: 20232000–84. However, good ethical standard will be adhered to [73,76].

The study is registered in the Region Directory, case number 23/54272.

Patients included in the study will give written informed consent according to the Declaration of Helsinki [77] with additional permission to publish data and results anonymously in scientific articles and to other relevant stakeholders.

## 3. Discussion

This study is a randomized controlled trial, which will test the effect of a Medication Coordinator in the transition of care between healthcare sectors. The Medication Coordinator will facilitate the medication reviews in close collaboration with patients applying motivational interview concepts in combination with *My Medication Plan*. A strength of this study is that the intervention is complex. The MRC framework allows flexibility and adaptability during the process of performing the complex intervention [5]. The complex intervention will be adapted based on the patient’s needs. Some patients want full involvement in every decision and aspect regarding their medication treatment. Meanwhile, other patients do not, but indeed wish to be informed about medication changes [78–80].

A primary outcome is selected to assess the overall effect of the intervention model. In the literature, several primary outcomes are used to report the effectiveness of medication reviews, and the effectiveness of the medication reviews are in consistent [39–41,81–83]. Primary outcomes often measured in randomized controlled trials when the intervention is a mediation review include mortality, acute readmissions, and PIMs [39,41,82]. These outcomes relate to patient safety and the optimization of a patient’s medication treatment. The performance and effects of a medication review may differ across healthcare settings and clinical pharmacist qualifications. Due to the complexity of a medication review, the effect may have many components [5] and might not be able to detect by one primary outcome The limitation of this complex intervention is the inability to assess which part of the intervention provided the effect or was most effective. It is impossible to identify one component of a complex intervention and implement only this. However, we can document the implementation of components by process measures.

The effect of a medication review not only depends on the different components of the intervention itself but is also highly dependent on the patient’s subjective experience [5,47]. Thus, the complex intervention model may have several positive effects, which we will assess using secondary outcomes like patient-reported quality of life and treatment burden. Some patients might find the medication review with the Medication Coordinator effective, but for others, the information passed onto the GP in the discharge summary may be more effective. Nevertheless, all components are a part of the complex intervention.

Because the resources in the healthcare sector are scarce, prioritizing the patients most in need of a medication review is a priority [84]. A Danish study in general practices has demonstrated that patients with a MERIS score above 13 would most likely benefit from a medication review [37]. The MERIS screening tool is based on patients’ renal function, the total number of medications, and the risk of harm or interactions caused by drugs [31,37]. These factors might be just as high a risk for experiencing an adverse drug-event as age. Age has been associated with increased risk of experiencing an adverse drug-event due to changes in pharmacokinetic and pharmacodynamic [85]. This may be explained by many drugs being renal excreted, hence may need dose-adjustments. These factors might indicate a risk for experiencing an adverse drug-event similar to age, which has been associated with increased risk of experiencing an adverse drug-event. This may be explained by many drugs being excreted renally, hence may need dose-adjustments. Therefore, there is a need to adjust the dose according to renal function. Patients of all ages are included in this study as younger patients could also have a high MERIS score and benefit from the intervention.

Another strength of this study is the intention to secure the information flow in the transition from the hospital to the patient’s home. Medication changes and follow-up appointments with healthcare professionals are presented to the patient by *My Medication Plan* and to the GPs via the electronic discharge summary.

A strength of the data generation process is that one person collects it. It can also be a limitation of the study as there is a risk of the Pygmalion Effect [86]. It is a limitation that the first author is performing the complex intervention.

Patients in both groups are included from the same ward, which might result in contamination bias [87]. The physicians treat patients from both groups and will likely adopt some medication-related learning. The physicians may apply this learning to some of the patients in the control group, resulting in an increased focus on the patient’s medication treatment. These limitations would bias the estimation of the effect towards no difference in relation to the null hypothesis.

Three questionnaires are to be answered by the patients, so there is a risk of transfer bias [88]. Patients might be particularly susceptible to loss of follow-up in Questionnaire 3, e.g. because they forget to answer or could pass away in the follow-up period. To avoid the loss of data, an intention-to-treat analysis is applied [89].

There is a risk for social-desirability bias in relation to the questionnaire [90,91], e.g., because the patients are answering what they think is expected of them. The same bias might occur during the medication review with the patients telling the Medication Coordinator what they think the Medication Coordinator requests to hear.

As hospitalized patients are often vulnerable, it can be difficult for them to answer a questionnaire. Especially if the questionnaires are long, they can be cognitively demanding. For this reason, the addition of the two VAS’s will capture patient-reported outcomes regarding quality of life and treatment burden.

### 3.1. Practical implications

This project may have the capability to provide a missing piece to a puzzle, i.e., the inclusion of GPs and *My Medication Plan* in this collaborative model. The Medication Coordinator could be a clinical pharmacist employed at a hospital or general practice. Hopefully, this can contribute to a reduction in the risk of post-hospital potentially inappropriate medication usage.

Patients in the intervention group are urged to become empowered and to take control over their medication treatment, as they are a part of the whole process that may increase their quality of life and reduce their treatment burden. Hence, the patient’s medication treatment quality is optimized, reducing the risk of drug-related problems.
